### Statistics and data analysis

The statistical analysis will be performed by the Clinical Research and Epidemiology Unit at the Montpellier University Hospital using SAS software (SAS Institute, Cary, NC, USA). The level of significance is set at *p* < 0.05 (bilateral).

Statistical analysis will be performed on the intention to treat (ITT) population. The decision to perform analyses on other population sets for sensitivity analysis will be taken by the study methodologist if necessary.

The number of screened, included, and randomized patients in each group will be summarized in a flow chart. Excluded and lost to follow-up patients will be reported.

Patients’ characteristics in the total population and in each group will first be analyzed. Quantitative variables will be expressed by mean, standard deviation, median, range, and quartiles. Qualitative and categorical data will be summarized by frequencies and percentages. Characteristics will be compared between the two groups using Student’s *t* test or Mann-Whiney *U* test for continuous variables and chi-square or Fisher exact test for categorical variables.

The distribution of the main outcome will be compared between the two groups with chi-square or Fisher exact test. Logistic regression models will also be implemented to analyze the effect of the group on the main outcome by adjusting on variables of interest. Univariate models will first be executed, and the variables with a *p* value lower than 0.15 will be considered for a multivariable model. Then, the variables with a *p* value lower than 0.05 in the multivariable model after a stepwise selection of variables will be considered statistically significant.

Categorical secondary outcomes will be analyzed using the same methodology as the main outcome, with chi-square or Fisher exact test and logistic regression models. Quantitative secondary outcomes will be compared between the two groups using Mann-Whiney *U* test, along with multivariable linear regressions with covariates of interest.

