### Randomization

Participants meeting the inclusion criteria are randomized by the ED pharmacist using a centralized computer generated randomization available on the e-CRF. Minimization randomization is used. Randomization (1:1) is stratified on the following criteria: type of ADE (linked to medication vs noncompliance), severity of the ADE (discharge from ED vs hospitalization), and age (± 70 years old).

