### Sample size

The study by Zhang M et al. showed 17% of hospital ADE readmission. This rate is based on data from medical coding which probably underestimate this rate [15]. A descriptive pre-study carried out in the study center to assess the impact of specific ADE alert to community health professionals in case of ADE showed a rate of emergency readmissions of 13.7% without transmission of the medico-pharmaceutical report and a rate of 5.1% with transmission. Assuming a 14% readmission rate in the control group and a rate of 5% in the TOC group, a sample size of 314 subjects is required with two-sided alpha = 0.05 and a power of 80%. To take into account a 10% dropout rate, 173 subjects per group will be included.

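### Allocation is minimised on three factors, but no stated analysis of the primary endpoint is certain to include them; the main test stays valid but may be conservative and slightly less powerful

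*Protocol article*

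**What the plan says.** In the section Randomization, the article states "Minimization randomization is used". The 1:1 allocation is balanced on "type of ADE (linked to medication vs noncompliance), severity of the ADE (discharge from ED vs hospitalization), and age", with age split at 70 years.

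In Statistics and data analysis, the main comparison is unadjusted: "The distribution of the main outcome will be compared between the two groups with chi-square or Fisher exact test". A second layer follows: "Logistic regression models will also be implemented to analyze the effect of the group on the main outcome by adjusting on variables of interest". The variables of interest are not named, and the entry rule is data-driven: "Univariate models will first be executed, and the variables with a *p* value lower than 0.15 will be considered for a multivariable model". Stepwise selection at 0.05 comes next. The section does not mention the three minimisation factors.

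The Sample size section uses two proportions and no covariates: "Assuming a 14% readmission rate in the control group and a rate of 5% in the TOC group", two-sided alpha of 0.05, 80% power and 314 subjects, raised to 173 per group for dropout.

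**The concern.** Minimisation makes the arms more alike on the chosen factors than simple randomisation would. If those factors predict the outcome, the true variance of the difference between arms shrinks. The ordinary chi-square still uses a variance that includes the outcome variation between factor levels, so it is too large. The test then rejects less often than its nominal 5% under the null, and less often than an adjusted test when there is a real effect.

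The logistic models could repair this if they always contained the factors, but the stated rule does not ensure it. A factor can be dropped because its p-value misses a threshold in this sample, even though it shaped the allocation. The rule does not expressly exempt the group term from selection either, although the purpose given for the models implies that it stays. At stake is some efficiency in a trial planned at 80% power, and an adjusted estimate whose covariates are settled only after the data are seen.

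**Working it through.** **1. The plan's own figure.** Inputs from Sample size: 14% and 5%, two-sided alpha 0.05, power 80%. The arcsine formula is n per group = 2(z₀.₉₇₅ + z₀.₈₀)² / h², with h = 2[arcsin√0.14 − arcsin√0.05].
- h = 2(0.3835 − 0.2255) = 0.316, so h² = 0.0998.
- (1.960 + 0.842)² = 7.849, so n = 2 × 7.849 / 0.0998 ≈ 157.2 per group.
- Rounded down, this is 157 per group, or 314 in total (316 if rounded up). The stated 314 is reproduced. Then 157 × 1.10 = 172.7, which gives the stated 173.

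**2. Power of the unadjusted test as planned.** Enumerating all outcomes of two binomials at 14% and 5%:

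| Per group | Pearson chi-square | Fisher |
|---|---|---|
| 157 | 79.6% | 74.0% |
| 173 | 83.8% | 78.0% |

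**3. What the factors change.** The article gives neither the prevalence of the factors, nor their association with readmission, nor the minimisation probability. Assumed here: prevalences of 30%, 40% and 50%, and a biased coin with probability 0.8. Total N is 314, with 8,000 simulated trials per setting. The null has 14% in both arms; the alternative has 14% against 5%. The adjusted test is the logistic score test for group with the three factors in the model.

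| Odds ratio of factors with outcome | Type I error, chi-square | Type I error, adjusted | Power, chi-square | Power, adjusted |
|---|---|---|---|---|
| all 1 | 5.0% | 5.1% | 79.4% | 79.8% |
| one factor at 2 | 4.6% | 4.9% | 79.7% | 80.2% |
| all 1.5 | 4.4% | 4.7% | 79.5% | 80.0% |
| all 2 | 4.3% | 4.8% | 79.3% | 80.5% |
| all 3 | 3.7% | 5.0% | 79.9% | 82.3% |
| all 4 | 3.4% | 4.9% | 80.3% | 84.1% |

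Monte Carlo error is about 0.45 points on power and 0.25 on type I error. A separate simulation with the same prevalences and coin agrees on direction and rough size. It gave chi-square type I error of about 4.6% with all odds ratios at 2 and 3.9% at 3. Power rose from 79.9% to 81.2% at 2 and from 79.3% to 81.6% at 3.

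**4. Does the stepwise rule keep the factors?** Univariate screening at 0.15 followed by backward elimination at 0.05 was simulated at N = 314 with 14% against 5%. The same prevalences were used, with simple 1:1 allocation and 600 trials per setting. All three factors were retained in 0.2% of trials when each odds ratio was 1.5, in 7.5% at 2, and in 43% at 3. None was retained in 55% at 1.5 and in 22.5% at 2. Under these assumptions the selected model usually lacks at least one minimisation factor, even when all three are truly prognostic.

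**The case against.** The strongest reply is that nothing here is an error. The sample size and the main test match: both compare two proportions without covariates. The chi-square never exceeds 5% beyond simulation error, and it delivers essentially the power that was planned. If all 346 randomised patients contribute an outcome, the exact figure is 83.8%. Adjusted models are already foreseen, and an unseen analysis plan may list their covariates. No prognostic strength is documented, so the gain from adjustment could be under 1 point.

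Most of this stands, and it limits the size of the point. It does not remove it. The article does not merely leave the covariates open: it states a selection rule by p-value, and that rule can discard the factors used for allocation.

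A reader might also infer that the mention of Fisher costs the trial 5.6 points of power (79.6 − 74.0). The text does not support that. Naming chi-square or Fisher is the usual wording for a small-count fallback. At the planned rates, 157 × 0.14 + 157 × 0.05 ≈ 30 events are expected, about 15 per arm. If the trigger is an expected count below 5 (an assumption), Fisher would need fewer than 10 events in total, a chance of a few in a million. The lower figure matters only if Fisher were used routinely, which the plan does not say.

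**Conclusion.** The mismatch between allocation and analysis is real, and its consequence is modest. The main test ignores the minimisation factors, and the additional models do not guarantee them. If the factors are prognostic, the chi-square is conservative: about 4.3 to 4.6% with all odds ratios at 2, 3.7 to 3.9% at 3, and 3.4% at 4. It gives up under 1 point of power for weak factors, about 1 point at odds ratios of 2, and about 2 to 4 points at 3 to 4. If the factors are not prognostic, there is practically no difference. All of these sizes depend on the assumed prevalences, odds ratios and coin probability.

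Two stronger readings are tempting. One is that the unadjusted test is invalid or falls short of its planned power; the exact 79.6% and the type I errors at or below nominal rule that out. The other is that a loss of several points is certain; that would require three strongly prognostic factors, which the article does not document. This is a worthwhile improvement in efficiency and pre-specification, not a flaw that threatens the conclusion.

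**What to change.** Name one primary analysis: the group effect from a logistic model containing type of ADE, severity and age group, coded as in the minimisation. Exempt these three factors and the group term from any p-value or stepwise selection. A Cochran-Mantel-Haenszel test over the cells of the three factors is an acceptable alternative. Keep the unadjusted Pearson chi-square as a supportive analysis. Any selection among further covariates should be labelled exploratory.

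Make the change before outcomes are examined by arm. The three factors have to be known at randomisation, which runs through the e-CRF, so no new data are needed. The cost is one line in the protocol and the analysis plan. The risk is negligible: even with no prognostic factor, simulated power was 79.8% adjusted against 79.4% unadjusted, and the adjusted type I error stayed between 4.7% and 5.1%.

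### The adjusted group effect is built by p-value screening and stepwise selection that protects neither the group term nor the minimisation factors

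*Protocol article*

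**What the plan says.** In the protocol article, Statistics and data analysis, the main outcome is first tested without adjustment: "The distribution of the main outcome will be compared between the two groups with chi-square or Fisher exact test". A second analysis follows: "Logistic regression models will also be implemented to analyze the effect of the group on the main outcome by adjusting on variables of interest". Those variables are not listed. They are to be found by fitting univariate models, carrying forward whatever reaches p < 0.15, and applying stepwise selection; variables with a p "value lower than 0.05 in the multivariable model after a stepwise selection of variables will be considered statistically significant".

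The rule then extends further: "Categorical secondary outcomes will be analyzed using the same methodology as the main outcome".

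Under Randomization, allocation is by minimisation: "Randomization (1:1) is stratified on the following criteria: type of ADE (linked to medication vs noncompliance), severity of the ADE", with age (cut at 70 years) as the third factor. The analysis section does not mention these factors again. It does not exempt them, or the group, from the screen or the stepwise step.

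**The concern.** The stated purpose and the stated procedure do not match. Estimating a randomised group's effect calls for a model fixed in advance with the group in it. A p-value screen followed by stepwise selection is a search for predictors. Used here, it has three consequences:

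- The covariate set is unknown until the outcomes are seen, and with few events it depends heavily on chance.
- The factors used to balance allocation enter the adjusted analysis only if their p values are small enough. The chi-square or Fisher test ignores them, so no stated analysis of a categorical outcome is sure to reflect the allocation scheme.
- Read literally, the group is one more variable to be screened. The adjusted effect, which is the reason for fitting the model, can then be absent from it.

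This is a rule that the article fixes, not a detail left to an analysis plan. A plan that prespecified covariates would contradict it.

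**Working it through.** **Inputs from the article.** The Sample size section sets the rates: "Assuming a 14% readmission rate in the control group and a rate of 5% in the TOC group". From these it derives 314 evaluable patients in total (two-sided alpha 0.05, 80% power), raised to 173 per group for 10% dropout. Statistics and data analysis: thresholds 0.15 and 0.05. The Outcomes section lists sociodemographic data, comorbidities, medications and ADE characteristics as collected, but gives no number of candidate covariates.

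**1. The plan's own sample size.** The arcsine formula is n per arm = 2(z₀.₉₇₅ + z₀.₈₀)² / h², with h = 2·asin√0.14 − 2·asin√0.05. It gives 157.2 per arm, 314.5 in total, which reproduces 314. Then 157 × 1.10 = 172.7, which gives 173 per group.

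**2. Expected events.** Events = n per arm × (0.14 + 0.05).
- 314 evaluable: 157 × 0.19 = 29.8
- 346 enrolled: 173 × 0.19 = 32.9

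**3. Events per parameter (intercept not counted).**

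| Model | Parameters | At 314 | At 346 |
|---|---|---|---|
| Group + 10 candidates (assumed) | 11 | 2.7 | 3.0 |
| Group + 20 candidates (assumed) | 21 | 1.4 | 1.6 |
| Group + 3 minimisation factors | 4 | 7.5 | 8.2 |

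Candidates unrelated to the outcome pass the screen at a rate of 0.15: 10 × 0.15 = 1.5, or 20 × 0.15 = 3.0.

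**4. Simulation with the group screened like the rest.** Assumptions: 157 per arm, 1,500 trials per scenario, 10 or 20 binary candidates of prevalence 0.4, three of them prognostic (log odds ratio 0.7 each), screen at 0.15, then backward elimination at 0.05. The article does not state the stepwise direction or stay level, so these are my reading. The covariates are centred on the logit scale, so average event rates run slightly above the nominal ones.

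| Rates | Group absent, 10 candidates | Group absent, 20 candidates | Unadjusted test significant |
|---|---|---|---|
| 14% vs 5% | 16.5% | 17.9% | 83.6%, 81.7% |
| 14% vs 9% | 71.2% | 69.7% | 28.7%, 29.9% |
| 14% vs 14% | 94.2% | 94.5% | 5.5%, 5.8% |

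A further run with 15 candidates extends the range at 14% vs 5% to about 21%. Absence is close to one minus power (for example 1 − 0.836 = 0.164 against 0.165): what goes missing is mostly the non-significant estimate.

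**5. Instability of the covariate set.** Across 1,500 trials the rule selected 110–119 distinct covariate sets with 10 candidates and 426–473 with 20. With 15 candidates, at least one pure-noise variable stayed in about 43–48% of trials.

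**6. Same selection with the group forced in (15 candidates).**

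| | Group forced, covariates selected | Prespecified model |
|---|---|---|
| Type I error | 0.055 | 0.048 |
| Power, 14% vs 5% | 0.797 | 0.798 |
| Median OR, 14% vs 5% (true 0.32) | 0.305 | 0.301 |

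A separate run at 14% vs 9% gave geometric mean ORs of 0.587 and 0.588.

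**7. Type I error.** With the group screened, or forced in alongside selected covariates, it was 0.055–0.059 in the runs of step 4. The Monte Carlo standard error is √(0.05 × 0.95 / 1500) = 0.0056, so 0.059 is (0.059 − 0.05)/0.0056 = 1.6 standard errors above nominal.

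**The case against.** The strongest reply is that the main comparison is untouched. The chi-square or Fisher test comes first, the trial is sized for two plain proportions, and the regression is introduced as an addition. That stands, and it limits the point to the adjusted analysis.

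A second reply is that the group is the exposure, so the variables being screened are naturally the ones adjusted for. This is a reasonable reading, and the sentence on the model's purpose favours it. The text permits dropping the group; it does not state it. Under this reading the group estimate hardly moves (step 6), and the absence figures do not apply. The outcome-driven covariate set and the unprotected minimisation factors remain.

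Four stronger conclusions are tempting, and the documents do not support them:

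- *That the rule exaggerates the odds ratio.* At 14% vs 5%, the mean OR among significant trials was 0.250 under the rule, 0.253 under a prespecified model and 0.264 unadjusted, against a true 0.32. Conditioning on significance produces this under every method.
- *That the group's p value loses its meaning.* Type I error is not materially inflated (step 7).
- *That a non-significant group effect will go unreported.* The article has no such rule, and the crude rates and the group's univariate model exist regardless. Only the adjusted estimate can be lost.
- *That the open-label design lets knowledge of allocation steer the model.* Outcomes are collected blind to arm.

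**Conclusion.** The point holds for the adjusted analysis only. The article states a treatment-effect aim, then fixes a procedure that lets about 30 events choose the covariates and guarantees a place to neither the group nor the three minimisation factors. The event count follows from the plan's own rates. The size of the effect on the model depends on assumptions about the number, prevalence and strength of candidates, and on the stepwise direction and stay level. If the group is screened, its adjusted estimate is absent in about 17–21% of trials at the planned effect and about 70% at 14% vs 9%. If it is always retained, the practical effect on its estimate is negligible.

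Severity: should-fix. The unadjusted primary test is valid as written, but the adjusted analysis, including that of the categorical secondary outcomes, needs a fixed specification.

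**What to change.** For the treatment-effect models, replace the screen and stepwise step with one prespecified logistic model of outcome on group, type of ADE, severity of ADE and age at the 70-year cut. State that the group is always retained and that its estimate and 95% CI are reported whatever the p value. Use the same model for categorical secondary outcomes where the number of events allows. Any stepwise search for risk factors becomes a separate analysis labelled exploratory.

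In simulation with the group and three fixed covariates (the prognostic ones, standing in for the minimisation factors), the group estimate is reported in every trial, type I error is 0.053–0.054, and power at 14% vs 5% is 0.82–0.84.

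The cost is a change of wording in the protocol and analysis plan, with no new patients or data. It should be made before outcomes are analysed. The downside is that an unanticipated strong predictor is left out of the main adjusted model; the exploratory analysis can still show it.

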### Missing data

The type of missing data will be determined for the main variables of interest. Conditional rejection of the hypothesis NMAR (not missing at random) and the assumption M.C.A.R. (missing completely at random) against MAR (missing at random) will be tested by studying the relationship between the variable status (missing or not) and the values of the covariates. If the missing data is type MAR or MCAR, a multiple imputation will be implemented [16]. When possible, missing data will be complemented by the deductive method from all of the variables collected. These multiple imputations will be used in the sensitivity analysis.

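### Multiple imputation is made conditional on ruling out NMAR by a covariate check that cannot do so, and neither outcome of that check leads to an analysis under NMAR

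*Protocol article*

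**What the plan says.** The Missing data section of the protocol article says that the type of missing data will be determined for the main variables. It announces a "Conditional rejection of the hypothesis NMAR (not missing at random") and a test of MCAR against MAR. The only tool it names is the relation between a variable's missing or observed status and the covariate values.

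It then sets a condition: "If the missing data is type MAR or MCAR, a multiple imputation will be implemented". Values that can be deduced from other collected variables are filled in where possible. On the role of imputation it says: "These multiple imputations will be used in the sensitivity analysis". No analysis is named for data classed as NMAR.

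Under Statistics and data analysis, "Statistical analysis will be performed on the intention to treat (ITT) population". The main outcome is compared by chi-square or Fisher exact test, and the methodologist may add sensitivity analyses on other population sets. The Outcomes section takes outcomes from calls to the patient at 3 and 6 months and to the general practitioner at 6 months, compared with the electronic medical file when available. Eligibility criteria counts loss to follow-up among the dropouts. Sample size plans for them: "To take into account a 10% dropout rate, 173 subjects per group will be included".

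**The concern.** MAR and NMAR differ in whether, given what was observed, missingness still depends on the value that was not seen. A regression of the missingness indicator on covariates uses observed values only. A clear association is evidence against MCAR. Neither an association nor its absence bears on MAR against NMAR. The plan nevertheless makes imputation depend on having excluded NMAR.

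The rule therefore gives no protection on either branch:

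- **Classed MAR or MCAR:** the missing-data sensitivity analysis is MI, which assumes MAR. Departure from MAR is not examined.
- **Classed NMAR:** imputation is withheld and no alternative is given, in the situation where a sensitivity analysis matters most.

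The design makes outcome-related or arm-related loss plausible. Follow-up is mainly by telephone, nonadherence is a qualifying event type, and only the experimental arm has the post-discharge call and the specific alert to the general practitioner, who is also an outcome informant. With few events expected, a handful of unseen outcomes could change the conclusion.

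**Working it through.** **Inputs.** The Sample size section gives event rates of 14% (control) and 5% (TOC), a two-sided 5% level, 80% power, 314 patients before dropout, 10% dropout and 173 per group. The Randomization section gives 1:1 allocation.

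**The plan's own figure.** The arcsine two-proportion formula gives 158 per arm, 316 in total, within 2 of the stated 314. Then 314 × 1.1 = 345.4, rounded up to 346 = 2 × 173. The sample size is not at issue here.

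**Step 1: what the observed data can say.** Assumption: 10% of 173, about 17 per arm, have no primary outcome, so 156 per arm are observed at close to the design rates: 0.14 × 156 ≈ 22 and 0.05 × 156 ≈ 8.

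- Observed cases: 22/156 = 14.1% against 8/156 = 5.1%. Pooled rate 30/312 = 0.0962; SE = √(0.0962 × 0.9038 × 2/156) = 0.0334; z = 0.0897/0.0334 = 2.69; p = 0.007.
- Range compatible with these data: control from 22/173 = 12.7% to 39/173 = 22.5%; TOC from 8/173 = 4.6% to 25/173 = 14.5%.
- Control minus TOC therefore lies anywhere from 12.7 − 14.5 = −1.7 points (from unrounded values) to 22.5 − 4.6 = +17.9 points. Covariates cannot narrow this without an assumption about the missing outcomes.

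**Step 2: how few events matter.** Give the missing controls 2 events (0.14 × 17 ≈ 2), so control is 24/173, and vary the missing TOC events:

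| Events among 17 missing TOC patients | TOC total | Difference (points) | p (chi-square, uncorrected) |
|---|---|---|---|
| 1 | 9/173 | 15/173 = 8.7 | 0.006 |
| 2 | 10/173 | 14/173 = 8.1 | 0.011 |
| 4 | 12/173 | 12/173 = 6.9 | 0.035 |
| 5 | 13/173 | 11/173 = 6.4 | 0.056 |

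For the last row: pooled 37/346 = 0.1069; SE = √(0.1069 × 0.8931 × 2/173) = 0.0332; z = 0.0636/0.0332 = 1.91. Significance is lost at 5 events of 17, about 30%, against about 5% among observed TOC patients.

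**Step 3: does the planned check see NMAR?** Illustrative assumption: 40% of patients with an event and 6.6% of those without are missing, in both arms, at 14% and 5%, with a covariate unrelated to outcome.

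- Control observed rate: 0.14 × 0.60 / (0.14 × 0.60 + 0.86 × 0.934) = 0.084/0.887 = 9.5%.
- TOC observed rate: 0.05 × 0.60 / (0.05 × 0.60 + 0.95 × 0.934) = 0.030/0.917 = 3.3%.
- Observed difference 6.2 points against a true 9.0, with about 10% missing overall.
- In 1,000 simulated trials, the test of missingness against the covariate rejected in 4.9%, its nominal level. The mechanism is NMAR and biases the estimate, yet the check is blind to it.

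**Step 4: direction.** Take true rates of 14% and 10%, with 40% loss among events and 7% among non-events. Where that loss applies, the observed rates become 0.084/0.8838 = 9.5% (control) and 0.060/0.897 = 6.7% (TOC). Against a true control-minus-TOC difference of 4.0 points:

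- loss pattern in TOC only: 14.0 − 6.7 = 7.3;
- in both arms: 9.5 − 6.7 = 2.8;
- in control only: 9.5 − 10.0 = −0.5.

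The bias can go either way, so the sensitivity analysis has to vary the arms separately.

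**The case against.** **The sentence may be clumsy English.** It could mean that, subject to NMAR having been rejected, MCAR is tested against MAR; the covariate check would then be used legitimately. That is a fair reading, but imputation would still hang on ruling out NMAR, with no valid means given and nothing planned if it is not ruled out.

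**Outcomes are not collected by patient calls alone.** The endpoint is itself an emergency visit, so the general practitioner or the hospital file may capture it when the patient cannot be reached. The planned 10% also covers consent withdrawal, death before discharge and long hospital stays. This stands: 17 missing outcomes per arm is an assumption and may be too many. It does not make the check valid.

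**An article leaves detail to the full protocol or SAP.** True of an absent tipping-point analysis taken alone. The point here is a stated rule that cannot work as written.

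Stronger readings that a reader might infer are not supported:

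- *The primary analysis is complete-case and contradicts ITT.* The article never says complete-case. It is an inference from confining MI to the sensitivity analysis, and would apply only after deductive fill-in. Analysing patients as randomised with some outcomes missing is not a plain contradiction of ITT.
- *MI is the only sensitivity analysis.* Other population sets are allowed; MI is the only one stated for missing data.
- *The plan would exaggerate the benefit.* This needs one chosen asymmetry of loss; the other patterns in the working shrink or reverse the difference.
- *MI should be the primary analysis.* With a single missing binary outcome and covariates unrelated to loss, MI under MAR gives essentially the observed-case answer, so it would not remove such bias.

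**Conclusion.** The concern holds for the stated condition. Observed covariates cannot exclude NMAR, so they cannot decide whether imputation is appropriate, and neither branch of the rule examines NMAR for the primary endpoint. As written, the flaw affects the missing-data sensitivity analysis; it does not alter the primary estimate or the sample size.

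The potential consequence is material. A result of p = 0.007 at the design rates would become p = 0.056 with 5 events among 17 missing TOC patients and 2 among 17 missing controls. This rests on the assumed 17 missing per arm and the design event rates; fewer missing outcomes would make the result sturdier. The loss percentages used to illustrate bias are assumptions with no basis in the article, and no direction of bias can be claimed.

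**What to change.** 1. Delete the determination of missingness type as a condition for imputation. Associations between missingness and covariates may still be reported as description.
2. Run the MI sensitivity analysis regardless, after deductive fill-in, with arm, the minimisation factors (type of event, severity, age), the 3-month outcome and hospital-file data in the imputation model.
3. Add an NMAR sensitivity analysis of the primary endpoint: a delta or tipping-point grid in which the event odds or counts among missing patients vary separately by arm, reporting where the conclusion changes.
4. State that the primary test uses observed outcomes after deductive fill-in, if that is what is intended.

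Making MI the primary analysis is optional and not needed to correct the error.

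The cost is revised wording and a little extra programming. The inputs are already collected and the sample size is unchanged. The change should be made before outcomes are analysed by arm.
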